**Figure 1 fig1:**
[figure not shown]
SPIRIT schedule.

**Figure 2 fig2:**
[figure not shown]
Research flowchart.

The study designates patients in the recovery phase and the chronic phase as the case group and healthy adults as the control group. Comprehensive assessments of patients will be conducted both before and after each GCST treatment step, using data from the healthy adult group as a reference. Time since stroke onset is defined as the interval between the index stroke date and baseline assessment. Participants are categorized into a recovery phase (3–6 months post-stroke) and a chronic phase (≥6 months post-stroke) (13). These time windows correspond to the late subacute and chronic stages of stroke recovery and reflect time-dependent neuroplastic and functional recovery processes (14). A parallel stroke control group receiving standard rehabilitation was not included in the present protocol. This decision was based on the absence of a standardized, consensus-based conventional rehabilitation pathway across participating centers and the highly individualized nature of current clinical practice. Instead, healthy participants were recruited to provide normative reference values for gait biomechanics and neuromechanical indicators. These reference data will be used to characterize recovery trajectories and deviations from physiological patterns in the stroke cohort. In addition, the longitudinal within-subject design and mixed-effects modeling approach will allow each participant to serve as his or her own control over time, partially mitigating the absence of an external stroke comparator.

Given that GCST interventions are implemented in a predetermined sequence, the study does not employ blinding. However, the start and end points of each intervention step are clearly defined by specific tests. The evaluation of treatment efficacy is based on quantitative indicators, which are free from subjective biases. The study adopts a sequential intervention design, allowing patients to commence treatment at a step that matches their functional capabilities and to progress through treatment in a stepwise manner. This approach is advantageous for maximizing the personalized effects of the treatment. To minimize heterogeneity, step skipping is not permitted. All participants are required to complete each step sequentially. Progression is based on predefined functional criteria, and the duration of each step is individually adjusted according to performance. The number of sessions and days required to complete each step are systematically recorded and treated as indicators of intervention exposure.

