**Methods and analysis:**

This multicenter, prospective, sequential study will recruit 180 hemiparetic stroke patients (recovery phase: 3–6 months; chronic phase: ≥6 months post-stroke) across four hospitals, along with 30 healthy controls. GCST is divided into a structured, stepwise intervention (steps A–E) implemented sequentially based on predefined performance criteria. Assessments will be conducted at baseline, after the completion of each intervention step, and at follow-ups. The primary outcome is the minimal knee flexion angle of the hemiparetic limb during the swing phase, quantified using the three-dimensional gait analysis. Secondary outcomes include gait, postural, neuromuscular, and functional measures. Outcome assessors will be blinded to participants’ stroke phase. Longitudinal data will be analyzed using linear mixed-effects models. Healthy controls will provide normative reference values.

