### Objectives

In hemiparetic stroke patients, postural control deficits are associated with central nervous system lesion sites and disease duration. The GCST enhances standing postural adjustment through sequential, plane-specific resistive adaptive modulation, thereby improving postural adaptation criticality (the dynamic capacity of the neuromuscular system to reorganize postural control under external perturbations). This process also modulates brain motor integration and restores the lower-extremity gait rhythm controlled by the CPG.

The objectives are as follows:

To analyze the relationship between postural control deficits and neural damage locations, as well as disease duration, to clarify the specific defects and causes of posture adjustment in hemiparetic stroke patients.To analyze the maximum angles and pulling forces that hemiparetic stroke patients can tolerate in each step and to reveal the adaptive critical state characteristics of postural control.To observe the effects of each GCST step in hemiparetic stroke patients on posture and gait parameters and to systematically assess the clinical efficacy of GCST.To monitor the changes in motor integration in hemiparetic stroke patients by synchronizing multiple muscles of the lower extremities to identify the mechanisms by which GCST optimizes gait patterns through posture adjustment training.

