### Inclusion and exclusion criteria

The inclusion criteria for patient participants in the study are as follows:

Patients diagnosed with unilateral cerebral infarction or hemorrhage by CT or MRI;First occurrence of stroke with a clearly documented stroke onset date and currently in either the recovery phase (3–6 months post-stroke) or the chronic phase (≥6 months post-stroke) at the time of enrollment (15);Patients aged between 40 and 70 years;Those able to cooperate during examinations and follow simple instructions;Those exhibiting lower-extremity motor function impairment and hemiparetic gait;Those with the ability to stand independently for 2 min (provide stable center-of-pressure measurements in static balance assessments) (16) or to complete more than five consecutive gait cycles to ensure reliable kinematic data in three-dimensional gait analysis (17); andThe non-affected side has no significant coordination impairments and has muscle strength above grade 4 (ensuring the ability to participate in weight-bearing postural training while minimizing fall risk) (18).

The exclusion criteria for patient participants in the study are as follows:

Cerebellar injury or significantly reduced muscle tone.History of lower-extremity nerve, muscle, or skeletal system diseases or surgeries.Presence of lower-extremity joint pain or exhibiting significant foot inversion, clonus, or requiring botulinum toxin injection prior to training.Currently participating in other clinical trials.Severe diseases such as high-risk epilepsy or major cardiac conditions.Poor compliance or inability to complete the study interventions.

The healthy control group will be matched to the stroke patients for sex, age, and body type. They must be free of lower-extremity nerve, muscle, or skeletal diseases; pain; or surgery, which ensures their data reflects a healthy state.

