### Statistical analysis

Statistical analysis will be performed using SPSS software (V.26.0). Data normality will be assessed using the Shapiro–Wilk test, and variance homogeneity will be evaluated using Levene’s test. Normally distributed continuous variables will be expressed as mean ± standard deviation, and non-normally distributed continuous variables will be presented as median (interquartile range). Descriptive statistics will be used to summarize baseline demographic and clinical characteristics.

All statistical analyses will be conducted using linear mixed-effects models (LMMs) to account for repeated measurements, individualized intervention exposure, and inter-individual variability. Participant identity will be included as a random intercept, and time (baseline, post-intervention, follow-up) will be specified as a fixed effect. The primary outcome will be modeled within this framework. For secondary outcomes and exploratory analyses involving multiple comparisons, the Holm–Bonferroni correction will be applied to control the family-wise error rate. The primary outcome will not be adjusted for multiplicity.

Stroke phase (recovery vs. chronic) and center will be included as fixed effects. Time-by-phase interactions will be examined to explore potential differences in longitudinal recovery trajectories between stroke phases. To address heterogeneity in intervention exposure inherent to the sequential adaptive design, cumulative training dose and step-specific duration will be incorporated as time-varying covariates. This approach allows adjustment for individual differences in progression speed and treatment intensity. In the presence of non-normal outcome distributions or convergence difficulties, generalized estimating equations (GEEs) with appropriate link functions will be conducted as sensitivity analyses to assess the robustness of the primary findings.

Missing data will be handled under the missing-at-random assumption using the maximum likelihood estimation inherent in LMMs, which allows inclusion of participants with incomplete follow-up data without listwise deletion. Sensitivity analyses will be conducted to assess robustness. Effect sizes will be reported as model-estimated mean differences with 95% confidence intervals. Standardized effect sizes (Cohen’s d) will also be calculated where appropriate to facilitate clinical interpretation.

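### Disease duration is a stated objective, but the analysis enters it only as a two-level split at 6 months, although exact time since stroke is available for every patient

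*Protocol article*

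**What the plan says.** Under Objectives, the first aim is "To analyze the relationship between postural control deficits and neural damage locations, as well as disease duration". The Background adds that it is unclear how the effects of the training steps vary with disease duration.

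The inclusion criteria require "First occurrence of stroke with a clearly documented stroke onset date" and admit patients "currently in either the recovery phase (3–6 months post-stroke) or the chronic phase (≥6 months post-stroke) at the time of enrollment". No maximum time since stroke is given.

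The Study design section (text below Figure 2) states: "Time since stroke onset is defined as the interval between the index stroke date and baseline assessment". The next sentence forms the groups: "Participants are categorized into a recovery phase (3–6 months post-stroke) and a chronic phase (≥6 months post-stroke"). The Abstract gives the same ranges: "recovery phase: 3–6 months; chronic phase: ≥6 months post-stroke".

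The Statistical analysis section places all analyses in linear mixed-effects models and says: "Stroke phase (recovery vs. chronic) and center will be included as fixed effects". Time-by-phase interactions are to be explored. No continuous term for time since stroke is listed.

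**The concern.** A two-level phase variable treats a patient at 3 months and one just short of 6 months as identical. It also treats a patient at 6 months and one several years after stroke as identical. The only contrast left is the average difference across one cut. Any gradient inside the chronic group, which may be the larger and certainly is the wider group, cannot be seen.

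At stake are the duration part of the first objective and the exploratory question of whether trajectories differ by duration. Both would be answered less precisely than the collected data allow. The estimated phase difference would also depend on how long after stroke the recruited chronic patients happen to be, which makes it hard to carry over to another population.

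A smaller defect lies in the same text. Six months falls in both ranges in the Abstract, the Study design section and the inclusion criteria, with no tie rule.

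**Working it through.** **1. The plan's own figure, to see whether phase enters it.** The Sample size estimation section gives a mean change of 1.2 degrees and an SD of change of 6.36, so dz = 1.2/6.36 = 0.1887. With one-sided α = 0.05 and power 0.80, the normal approximation is ((1.645 + 0.842)/0.1887)² ≈ 174, the stated number (175 with the exact noncentral t). Phase plays no part, so nothing below changes this number.

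**2. Information kept by the split.** For a linear relation with a duration variable X, the share of information kept by the indicator (time ≥ 6 months) is the squared correlation between X and the indicator. If X is uniform and a share p lies below the cut, this equals 3p(1 − p).

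The documents give no distribution of time since stroke, so each one below is an assumption.

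*Log scale, log-uniform from 3 to M months.* Here p = ln(6/3)/ln(M/3).

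| M (months) | p | 3p(1 − p) | Equivalent patients out of 180 |
|---|---|---|---|
| 12 | 0.50 | 0.75 | 135 |
| 24 | 0.33 | 0.67 | 120 |
| 60 | 0.23 | 0.53 | 96 |

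On these assumptions the split costs as much as losing 25–47% of the sample for this question.

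*Raw scale, uniform.* From 3 to 9 months: p = 1/2, 75% kept. From 3 to 12: p = 1/3, 67%. From 3 to 24: p = 1/7, 3 × (1/7) × (6/7) = 37%.

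*3 months plus an exponential time (simulation, 2 million draws).* For exponential means of 6, 12 and 24 months, the share kept is 39%, 22% and 12% on the raw scale and 63%, 50% and 37% on the log scale.

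The full range is therefore about 12–75%. The low end comes from long right tails on the raw scale.

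**3. Size of the tie at 6 months.** Assume 180 patients, time since stroke uniform over 3–12 or 3–24 months, and 30.44 days per month.

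- Exactly one day in both groups: 180 × 1/(9 × 30.44) = 0.7 patients, or 180 × 1/(21 × 30.44) = 0.3. Both are under 1%.
- If 6 months could be read as any day in a 4-day range: 2.6 or 1.1 patients (1.5% or 0.6%).

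**The case against.** **The phases have a rationale.** The Study design section ties them to the late subacute and chronic stages of recovery. If the true relation is a step at about 6 months, the split loses little and the linear calculation does not apply. This stands as a limit on the size of the loss. The protocol does not show that the relation is a step, and a continuous term beside the phase summary would let the data speak to it.

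**The analysis of each objective may sit in a document not shown.** An SAP could add continuous duration. That is fair, but the article fixes a form for duration, and the form it fixes is the binary one. The point concerns that choice, not an omission.

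**Stronger readings that the documents do not support:**

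- *Two conflicting reference dates.* A reader might set "the chronic phase (≥6 months post-stroke) at the time of enrollment" against the baseline date in the Study design section. The first is an eligibility rule that admits either phase, so crossing 6 months between the two dates cannot change eligibility. The second alone dates the grouping variable. No gap between enrolment and baseline is stated.
- *A large ambiguous band.* If time were recorded in completed months, the band from 6 to 7 months would hold ln(7/6)/ln(M/3) = 11.1%, 7.4% or 5.1% of patients for M = 12, 24 or 60. The protocol instead defines an interval between two dates and requires a documented onset date, which points to counting in days.
- *Discretionary group membership with consequences for treatment.* All patients start at the same step and progress by predefined criteria. No treatment decision depends on phase.
- *Phase interaction in every model.* The time-by-phase terms are described as exploratory. They are not specified for every model.
- *Damage to the primary result.* The sample size rests on a paired pre–post change and makes no use of phase.

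**Conclusion.** The point holds for the disease-duration question. The stated analysis reduces an exactly derivable quantity to two levels with an open upper group and discards all within-group information on it.

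The loss is about 25–47% if the relation is linear in log time and onset times are log-uniform from 3 to 12–60 months. Over all the distributions tried, it is about 25–88% (12–75% kept). These figures rest on assumed distributions and an assumed linear form, so they show the order of the loss and do not estimate it.

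The shared 6-month boundary is a wording slip, worth correcting but probably affecting fewer than 1% of patients when dates are used. The primary comparison and the sample size stand. Overall this is a cheap improvement.

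**What to change.** **Statistical analysis section.** For the disease-duration question, enter continuous time since stroke to the baseline assessment (for example on the log scale) and its interaction with time. With baseline as the reference time, the main effect addresses the first objective when postural measures are the outcome. The interaction addresses whether trajectories vary with duration.

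Keep the two-phase comparison for presentation, in a separate model. Under the log-uniform assumptions, phase and log time correlate at √0.53 to √0.75, that is 0.73 to 0.87, so putting both in one model would blur each.

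**Abstract, Study design and inclusion criteria.** Write recovery as at least 3 and less than 6 months and chronic as 6 months or more. Count in days to the baseline assessment, as the Study design section already defines, and state once how months convert to days.

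**Cost.** One extra term and its interaction, from data already required for entry, plus wording in three places. The downside is an assumed functional form, which should be stated in advance. No new assessments and no change in sample size are needed.

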### Inclusion and exclusion criteria

The inclusion criteria for patient participants in the study are as follows:

Patients diagnosed with unilateral cerebral infarction or hemorrhage by CT or MRI;First occurrence of stroke with a clearly documented stroke onset date and currently in either the recovery phase (3–6 months post-stroke) or the chronic phase (≥6 months post-stroke) at the time of enrollment (15);Patients aged between 40 and 70 years;Those able to cooperate during examinations and follow simple instructions;Those exhibiting lower-extremity motor function impairment and hemiparetic gait;Those with the ability to stand independently for 2 min (provide stable center-of-pressure measurements in static balance assessments) (16) or to complete more than five consecutive gait cycles to ensure reliable kinematic data in three-dimensional gait analysis (17); andThe non-affected side has no significant coordination impairments and has muscle strength above grade 4 (ensuring the ability to participate in weight-bearing postural training while minimizing fall risk) (18).

The exclusion criteria for patient participants in the study are as follows:

Cerebellar injury or significantly reduced muscle tone.History of lower-extremity nerve, muscle, or skeletal system diseases or surgeries.Presence of lower-extremity joint pain or exhibiting significant foot inversion, clonus, or requiring botulinum toxin injection prior to training.Currently participating in other clinical trials.Severe diseases such as high-risk epilepsy or major cardiac conditions.Poor compliance or inability to complete the study interventions.

The healthy control group will be matched to the stroke patients for sex, age, and body type. They must be free of lower-extremity nerve, muscle, or skeletal diseases; pain; or surgery, which ensures their data reflects a healthy state.

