### Sample size estimation

The sample size calculation was based on an internal pilot dataset (n = 30) collected at the coordinating center prior to trial registration, using the minimal knee flexion angle during the swing phase on the hemiparetic side as the primary outcome measure. The pilot study was approved by the Medical Ethics Committee of the Affiliated Changshu Hospital of Soochow University (Approval No. X202265), and pilot participants were not included in the current trial (19). The use of pilot data to inform feasibility and parameter estimates for subsequent studies is supported by methodological guidance on pilot studies and pilot-informed trial planning (19, 20).

In the pilot dataset, the mean pre–post change in the primary outcome was 1.2 degrees, with a standard deviation of the within-subject change score of 6.36. The standardized effect size was therefore d = 0.1887 (d = Δμ/SDΔ). Although the pilot-derived effect size was small, the minimal knee flexion angle represents a joint-level biomechanical marker of neuromuscular coordination (21). Variations in swing-phase knee flexion primarily reflect changes in limb advancement mechanics and inter-joint coordination rather than global functional performance. Therefore, even relatively small angular differences may provide meaningful biomechanical information relevant to post-stroke gait recovery. Sample size estimation was performed using G*Power (difference between two dependent means, matched pairs). With an effect size (dz) of 0.1887, a one-sided significance level (*α*) of 0.05, and statistical power (1−β) of 0.80, the required minimum sample size was calculated to be 174 patients. A one-sided test was adopted, given the directional hypothesis that GCST would improve, rather than worsen gait performance. To account for potential attrition and to ensure balanced recruitment across centers, the planned recruitment target was set at 180 participants across four participating centers (approximately 45 participants per center). Based on pilot observations and adherence-enhancing procedures implemented in the study protocol, the anticipated attrition rate is expected to remain low. Healthy controls were not included in the sample size calculation and were recruited solely to provide normative reference values.

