**Figure 3 fig3:**
[figure not shown]
Diagram of the GCST steps.

Given that all participants are unilateral hemiparetic, the training commences at step B. Each step utilizes overlapping motor tasks and incremental difficulty to progressively unlock the patients’ potential. Progression from one GCST step to the next is based on predefined performance criteria rather than therapist discretion. Upon passing the step E test, the treatment cycle is concluded. Throughout the treatment, the number of days taken to complete each step is recorded. Each step is implemented at the patient’s maximum tolerable intensity. Once the criteria for progression are met, the next step is initiated immediately. Specific operational details are provided in Figure 2. Intervention sessions are terminated if participants experience dizziness, excessive fatigue (Borg scale > 15), unstable blood pressure, pain exacerbation, or an inability to maintain a safe standing posture. Safety monitoring is performed continuously during training. To ensure treatment fidelity across centers, a standardized intervention manual has been developed. Sessions are documented using structured fidelity checklists. A random 10% of sessions are video recorded (with patient consent) and reviewed by an independent senior investigator. Deviations from the protocol are documented, and corrective feedback is provided.

All hemiparetic stroke patients will receive conventional treatments based on clinical guidelines. They can participate in upper-extremity training, sitting balance exercises, lying-position training, stretching programs, and physical therapy as needed. However, strength training or motor skill training related to standing and gait functions is expressly excluded.

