### Data collection and management

Primary outcome indicators will be collected using standardized instruments to ensure data accuracy and objectivity. Secondary outcome indicators will be assessed independently by two professional therapists, with results cross-verified. Any discrepancies will be discussed to reach a consensus.

For patients who withdraw or change their training regimen, the time and reasons for withdrawal will be documented to determine whether their data will be included in the final analysis. If corrections are needed for original records, a dated statement explaining the changes must be attached. All original study documents and copies will be stored for inspection.

Data entry will use an electronic data capture system with double data entry to minimize errors. Each participant’s electronic case report form will be backed up. Project administrator accounts will be created to ensure that researchers have appropriate data access permissions based on their roles, responsibilities, and confidentiality agreements. Data uploaded from each center will be monitored by a third-party quality control organization (The Fourth People’s Hospital of Kunshan).

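### The compliance-and-completion exclusion has no assessment time and, with the withdrawal rule, permits enrolled non-completers to be left out once their course is known

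*Protocol article*

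**What the plan says.** In the protocol article, the list headed "The exclusion criteria for patient participants in the study are as follows" (Inclusion and exclusion criteria) ends with "Poor compliance or inability to complete the study interventions". The item does not say when or how it is judged, or whether expected or observed conduct is meant. Two other items in the same section do carry a time: stroke phase is judged at enrolment, and the botulinum toxin item refers to the period before training. Cooperation at screening is already an inclusion criterion: "Those able to cooperate during examinations and follow simple instructions".

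Elsewhere, completion is something that happens in the study. Study design states: "All participants are required to complete each step sequentially". Intervention states: "Progression from one GCST step to the next is based on predefined performance criteria rather than therapist discretion", and "Upon passing the step E test, the treatment cycle is concluded". Participant compliance describes measures to support compliance while the trial runs.

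For patients who withdraw or change their training regimen, Data collection and management states that "the time and reasons for withdrawal will be documented to determine whether their data will be included in the final analysis". Statistical analysis plans maximum likelihood under missing-at-random, which keeps participants with incomplete follow-up. Sample size estimation gives no attrition rate and says only that "the anticipated attrition rate is expected to remain low".

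**The concern.** An exclusion criterion should describe something that can be established before a patient enters. This one refers to conduct during the study interventions, which no candidate has yet received. Because it has neither a time nor a test, it can be applied after training has begun. The withdrawal rule points the same way, since it settles whether data are used after the reasons for stopping are known.

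The design makes this important. Stroke patients form a single treated cohort without a stroke comparator, and the planned test is a one-sided pre-post comparison with an expected change of 1.2 degrees against a standard deviation of 6.36. If patients who do poorly or stop are left out, no control arm loses patients in a similar way, so the selection passes straight into the estimated change. Reported attrition would be lowered too.

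**Working it through.** **The two rules side by side.**
- The exclusion names compliance and completion, without a time.
- Study design and Intervention make completion depend on passing successive performance tests, so it is known only during or after training.
- A purely prospective reading is possible, but it would largely repeat the cooperation inclusion criterion and has no stated basis for judgement.
- The withdrawal rule leaves the use of data open until the reason for stopping is known.
- Maximum likelihood uses incomplete records only from patients who are in the dataset. It does nothing for a patient left out of it.

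**The plan's own figure.** Inputs from Sample size estimation: mean change 1.2, SD of change 6.36, one-sided alpha 0.05, power 0.80, required n 174, target 180.
- dz = 1.2/6.36 = 0.1887.
- The normal approximation ((z_0.95 + z_0.80)/dz)² gives 174. The exact noncentral-t calculation gives 175. The stated 174 is reproduced within that tolerance.
- Margin: 180 − 174 = 6 patients, and 6/180 = 3.3%.

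No non-completion rate and no expected change in non-completers are given. Everything below rests on assumed values.

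**Illustration 1: dilution.** Assume completers change by 1.2 degrees, a fraction q do not complete and change by 0, and all of these are removed. The mean over all starters is 1.2 × (1 − q).

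| q | True mean, all starters | Reported | Ratio |
|---|---|---|---|
| 0.10 | 1.2 × 0.90 = 1.08 | 1.2 | 1.2/1.08 = 1.11 |
| 0.30 | 1.2 × 0.70 = 0.84 | 1.2 | 1.2/0.84 = 1.43 |

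**Illustration 2: no true change.** Assume the mean change over all enrolled patients is 0, the removed fraction f averages −k degrees, and the SD stays at 6.36 in those who remain. The remaining patients then average f·k/(1 − f). The rejection rate is that of the one-sided 5% paired t-test.

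| f | k | n left | Apparent change | Rejection rate |
|---|---|---|---|---|
| 0.10 | 1.2 | 162 | 0.12/0.90 = 0.13 | about 8% |
| 0.20 | 1.2 | 144 | 0.24/0.80 = 0.30 | about 14% |
| 0.10 | 3 | 162 | 0.30/0.90 = 0.33 | about 16% |
| 0.20 | 3 | 144 | 0.60/0.80 = 0.75 | about 41% |

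**Power.** If dz stays at 0.1887, removing 10%, 20% or 30% of 180 leaves 162, 144 or 126 patients, with exact one-sided power of 77.2%, 72.9% or 67.8%. Lost power is the smaller problem; the shift in the mean is the larger one.

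**The case against.** The strongest reply is that the item stands in a list of entry criteria and should be read as one. Candidates are inpatients, so a recruiting physician may already know of poor adherence or physical inability. Events after enrolment have their own provisions: the recruitment target allows for attrition, withdrawals are documented with time and reason, and the mixed model keeps incomplete records. No sentence tells a site to turn an enrolled patient into a screening exclusion.

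Much of this stands, and it rules out several stronger inferences that a reader might draw:
- That the criterion can be known only after training starts. A screening forecast is possible; the text simply does not say that this is meant.
- That sites will relabel non-completers as ineligible. The documents permit omission but do not direct it.
- That recorded attrition would be near zero. The provisions for withdrawal and incomplete data speak against this.
- That physicians would select likely responders. Predicted compliance is not predicted response, and a forecast at screening limits generalisability without biasing the within-patient change in those enrolled.
- That the criterion distorts days per step. Time to complete a step can come only from those who complete it, with or without this item.

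The numerical objection also stands. Zero change in non-completers is doubtful, since a patient who stops at a later step has finished earlier ones and has assessments from them. Nor is the pilot mean of 1.2 degrees described as a mean in completers.

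The reply does not remove the ambiguity. The provision for withdrawals is the one that makes use of the data depend on the reason for stopping, so it cannot serve as the safeguard.

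**Conclusion.** The point holds in a limited form. The criterion has no assessment time or objective basis and is worded as conduct during GCST. Combined with the withdrawal rule, it leaves room for enrolled non-compliers or non-completers to be omitted after their course is known. In a single-cohort pre-post study, such omission would bias the primary change and the reported attrition, and maximum likelihood could not undo it.

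Its size cannot be derived from the documents. The overstatement of 11–43% requires 10–30% non-completion, zero change in non-completers, a change of 1.2 degrees in completers, and removal of every non-completer. The rejection rates of about 8% to 41% require the assumed mean changes of −1.2 or −3 degrees in those removed. These figures show only that an expected change of 1.2 degrees is small enough to be affected by selective omission. They do not predict what the trial will report. The documents also do not support saying that the results are favourable by construction. The repair is well worth making because it costs little.

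**What to change.** 1. Delete the item, or replace it with facts verifiable before baseline, for example agreement to the five-times-weekly schedule and availability for follow-up.
2. State that eligibility is fixed before the first GCST session.
3. State that all enrolled patients with a baseline assessment enter the mixed model, and that later non-compliance or failure to complete is reported as an outcome and never used as an exclusion.
4. Align Data collection and management with this: time and reason of withdrawal are recorded for reporting and sensitivity analyses, not to decide whether data are used.

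The cost is a few sentences in the eligibility, data-management and analysis sections. No treatment step or progression rule changes. The downside is a possibly higher reported attrition rate and a smaller estimated change.
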